##### Delayed post-assessment

Three months after the post-assessment data collection is complete, parents will again be asked to evaluate the ongoing effectiveness of ATTACH provide observational, and questionnaire to evaluate the ongoing effectiveness of ATTACH^TM^.

#### Objective 2

NPT interviews will begin as soon as the first family completes the ATTACH^TM^ Reflective Function Intervention Phase and will continue until data saturation is attained, i.e., the degree to which new data repeats or is redundant with what was expressed in previous data [92]. We will employ a stopping rule: Data collection in a category (patient, health and social service providers, and health care administrator) will cease when three interviews in a row offer less than 5% new information (i.e., only one new code to one question of 19 in interview guide offers new information).

### Sample size {14}

#### Objective 1

##### Quantitative component

We will recruit until we have completed all study components with 100 new families, a sufficient *n* to detect minimum *d* = .34 for pre- /post- assessment differences in parent-child relationship quality. From discussions with agency health and social service providers and administrators, it will be feasible to recruit 30 families (including parents, co-parents, and children) from each agency, from patients currently seeking service, to retain 20 of them for 3 months postintervention for follow-up (any longer was deemed unrealistic given potential for patient relocation). Specifically, iKT and end-of-grant dissemination will be planned in partnership with agency health and social service providers and administrators.

#### Objective 2

##### Qualitative interviews guided by NPT

From discussions with agency administrators, it will be feasible to recruit 20 patients, 20 health and social service providers and 20 administrators (total *n* = 60) for interviews. However, recruitment and data collection will continue only until theoretical data saturation.

### Recruitment {15}

#### Objective 1

##### **ATTACH**^TM^**impacts**

Every partner agency (including additional agencies) will recruit 2–5 staff members for ATTACH^TM^ training to become the ATTACH^TM^ facilitators. To partake in the ATTACH^TM^ parenting program, participants will be identified through partner agencies. We will intervene with up to 150 parents and their birth to 36-month-old children to retain 100, from 5 community agencies. Parents will be recruited from rosters of patients currently seeking service. The ATTACH^TM^ information sheets and brochures will be posted on implementation sites. Their current and interested clients will be our potential participants. Their staff will assist with recruitment as participants seek their services in routine care.

#### Objective 2

##### ATTACH^TM^ implementation feasibility

Patients, health and social service providers and administrators from each of the five initial agencies will be recruited via convenience sampling methods. We anticipate 4 patients, 4 health and social service providers, and 4 decision makers will be recruited for interviews from each agency, for a total of 20 participants in each category.

## Methods: data collection, management, and analysis

### Data collection methods {18a, 18b)

#### Objective 1: ATTACH^TM^ impacts

We have engaged with our agency partners on the collection of parents’ and children’s demographic information, descriptive data on exposure to toxic stressors, outcome measures, and covariates. To reduce participant burden, data on demographic variables will be obtained from agency administrative records as much as possible (e.g., ethnicity, sex, and gender, first language, marital status, education, employment, number of children, and age of patients and children) at pre-assessment. To further reduce burden, many measures have been selected from intake data collection already conducted in agencies, e.g. ASQ-3 [84]. Covariate measures will primarily be those already given at patient intake and that focus on toxic stress exposures, i.e. depressive symptoms [Edinburgh Depression Scale (EDS) [93, 94], a 10-item self-report tool to measure depression and exhibits sensitivity of 66.7–69% and specificity of 67.7% and takes 5 minutes to administer], family violence [Revised Conflict Tactics Scale-Short Form (CTS2-SF) [95], a 20-item questionnaire with internal consistency of 0.79–0.95 and takes 3 minutes to complete], addictions [Alcohol, Smoking and Substance Involvement Screening Test (ASSIST) [96], a measure of dependence on cannabis, cocaine, and other drugs over lifetime and past 3-months, with high levels of internal consistency, construct, concurrent and discriminant validity [97] and takes 15 minutes to complete]; and adverse childhood experiences [Adverse Childhood Experiences (ACE) [98] Questionnaire, consisting of 10 questions, with extensive reliability and validity data and takes less than 3 minutes to complete]. To get at patient strengths in the face of toxic stress, the Brief Resilience Scale (BRS) [99] will also be administered, a 6-item tool that with internal consistency ranging from .80–.91 and takes 3 minutes to complete. All questionnaire data will be collected at pre-assessments, post-assessments and at 3 months post-assessment follow-up by agency health and social service providers /ATTACH^TM^ interventionists, who will be trained and supervised to do so on REDCap (www.project-readcap.org) as part of the ATTACH^TM^ training program. Please see Additional file 3: Appendix 3 for Dried Blood Samples (DBS) Protocol for DBS collection.

### Data management {19}

Partner agencies will collect the data on REDCap provided by the University of Calgary (https://redcap.ucalgary.ca/) via iPads with REDCap software already installed. Agency health and social service providers /ATTACH^TM^ interventionists will be trained and supervised to employ the iPads and REDCap (www.project-redcap.org) as part of the ATTACH^TM^ training program. Partner agency health and social service providers /ATTACH^TM^ interventionists will be provided with a login information access the pre-, post-, and delayed post-assessment questionnaires. After logging in, they will ask the participant to fill out the questionnaires, which will only request de-identified data (except for required linkage to consent, filed separately); data will be automatically shared to the REDCap website after completion. Any data sharing or communication from the partner agencies will be done via the University of Calgary domain specific email account. Digital video data will be saved on the iPads and uploaded to secure Box on the cloud (https://www.box.com/en-ca/capture). The staff at the local agencies will be trained/ instructed to delete any digital data from the iPads. Digital copies of transcripts and audio-files will be kept in a secure network location administered by the University of Calgary’s IT services and accessible only to the research team.

All the information contained in our analyses and summaries will be anonymous and based on group data. Any report published as a result of this study will not identify the participants by name, address, or any other personal information. Furthermore, all research team members are aware of the importance of maintaining participant anonymity and are required to sign a confidentiality agreement.

### Statistical methods {20a, 20b and 20c}

We will analyze the demographic characteristics of the sample with measures of central tendency and frequencies as appropriate. For all analyses, alpha will be set a priori at .05 (two-tailed).

#### Objective 1: ATTACH^TM^ impacts

For (1a), Evaluate ATTACH^TM^ impacts on parent-child relationship quality (primary outcome), parental RF, and child development and (1d) evaluate long-term impact of ATTACH^TM^ (3 months delayed post-assessment), we will employ repeated measures analysis of variance (ANOVA), paired-t-tests, and chi-square tests to examine outcomes between pre-assessments, post-assessments and at 3 months post-assessment follow-up. For (1b) Determine whether ATTACH^TM^ is equally effective across patient populations (and for whom it works best/worst), we will examine differences among sub-groups derived from known covariates through use of independent samples *t*-tests (two groups, e.g., child sex), ANOVAs (more than 2 groups, e.g., race/ethnicity), repeated measures analysis of covariance (with identified covariate) and linear regression models (continuous covariate, e.g., age, years of education). For (1c) evaluate whether ATTACH^TM^ impacts immune biomarkers indicative of inflammatory disease risk, (i.e., gene expression, DNA methylation).

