ATTACH^TM^ is a psychoeducational parenting program delivered in community agencies that serve families with preschool-aged children affected by toxic stress [18]. It was tested in seven rapid-cycling pilot studies with small sample sizes (*n*’s = 10–20 per pilot). Pilots were guided by the IDEAS (Innovate, Develop, Evaluate, Adapt, Scale) Framework^TM^ [18], an innovative clinical trial approach that reduces time from program development to implementation, while ensuring rigour in evaluation [18, 19]. In two phases, we conducted randomized control trial (RCT) and quasi-experimental (QE) pilot studies. In the first, phase, three pilot studies revealed that ATTACH^TM^ significantly improved parent-child relationship quality (*d* = .34–1.5) [9] parents’ RF scores (*d* = .51–2.0) [10], and children’s cognitive and motor development(*d* = .98–2.3; all *p*’s < .05) [9, 10]. These findings led the Harvard Center on the Developing Child to recognize and fund ATTACH^TM^ as a Frontiers of Innovation project (see https://developingchild.harvard.edu/innovation-application/frontiers-of-innovation/), supporting phase two. In the four pilot studies that followed, ATTACH^TM^ significantly improved parent-child interaction quality (*d* = .41–1.5), parental reflective function (*d* = 1.2–1.4), attachment security (eta^2^ = .30–.47), child development (*d* = .47–1.4; all *p*’s < .05) and immune cell gene expression [20, 21]. While these preliminary results are promising, whether ATTACH^TM^ is as effective when delivered by trained agency health and social service providers rather than researchers (as in the first seven pilot studies), in naturalistic community settings remain to be seen.

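### The tests named for the primary outcome, and the n = 100 statement, make no allowance for correlated change among families who share a facilitator

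*Protocol article*

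**What the plan says.** Statistical methods {20a, 20b and 20c} fixes the tests for Objectives 1a (which contains the primary outcome) and 1d: "we will employ repeated measures analysis of variance (ANOVA), paired-t-tests, and chi-square tests to examine outcomes" across the three assessments. The same section adds "For all analyses, alpha will be set a priori at .05 (two-tailed"). No facilitator or agency term, mixed model, cluster-robust error or ICC appears anywhere in the article.

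Sample size {14} says "We will recruit until we have completed all study components with 100 new families", described as "a sufficient *n* to detect minimum *d* = .34 for pre- /post- assessment differences". It gives no power, standard deviation, pre/post correlation or design effect. The .34 equals the lower end of the phase-one pilot range in Background and rationale: "significantly improved parent-child relationship quality (*d* = .34–1.5").

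On staffing, Recruitment {15} says that every partner agency "will recruit 2–5 staff members for ATTACH" training as facilitators, and the Intervention section gives a minimum of two per agency. Study setting {9} counts 4 initial agencies; Recruitment {15} counts 5. Sessions are led by a facilitator and are mostly one-to-one.

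**The concern.** A paired t-test or a standard repeated-measures ANOVA handles correlation between visits of the same family. It assumes that one family's change tells nothing about another's. Here several families work with the same facilitator, and facilitators may differ in how much change they produce.

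Pairing removes stable differences in level between facilitators. It does not remove differences in mean change, and mean change is what the trial estimates. Any such variation goes into the true standard error but not into the one that the named tests report.

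This matters more than usual for two reasons. Background and rationale presents the open question as whether the programme still works when agency providers rather than researchers deliver it, so variation between providers is part of the uncertainty in the answer. There is also no control group, so the primary inference rests on this one standard error.

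**Working it through.** **Inputs from the article.** Two-sided alpha .05; 100 families; d = .34; 2 to 5 facilitators per agency; 4 or 5 agencies; 20 retained families per agency.

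**Assumptions.** The ICC of change is taken as .02 to .10. All trained staff deliver, with equal caseloads. d is on the scale of the SD of change.

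**1. The plan's own figure.** With a paired t-test on 100 independent families, the noncentrality is .34 × √100 = 3.4 with 99 df, and power is 92%. Required n is 70 for 80% power and 93 for 90%. Because no power is stated, the 100 cannot be reproduced as the result of a calculation, but under independence it is enough for either target. If d is instead on the raw SD, power depends on the pre/post correlation: 66% at 0, 81% at .3, 92% at .5 and 99% at .7.

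**2. Families per facilitator (m).** Fewest facilitators: 4 × 2 = 8, so m = 100/8 = 12.5. Most: 5 × 5 = 25, so m = 100/25 = 4. Five agencies at the minimum of two give 10 facilitators and m = 10.

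**3. Effect of correlated change.** The design effect is DEFF = 1 + (m − 1) × ICC, and effective n = 100/DEFF. The true type I error of the unadjusted test is about 2 × [1 − Φ(1.984/√DEFF)]. Example, m = 10 and ICC .05: DEFF = 1 + 9 × .05 = 1.45; effective n = 69; 1.984/√1.45 = 1.648; type I error 9.9%.

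| Facilitators (m) | ICC | DEFF | Effective n | Type I error, named test | Power at d = .34, design effect only | Power with (facilitators − 1) df |
|---|---|---|---|---|---|---|
| 25 (4) | .02 | 1.06 | 94 | 5.4% | 91% | 89% |
| 25 (4) | .05 | 1.15 | 87 | 6.4% | 88% | 86% |
| 25 (4) | .10 | 1.30 | 77 | 8.2% | 84% | 82% |
| 10 (10) | .02 | 1.18 | 85 | 6.8% | 87% | 80% |
| 10 (10) | .05 | 1.45 | 69 | 9.9% | 80% | 71% |
| 10 (10) | .10 | 1.90 | 53 | 15.0% | 68% | 60% |
| 8 (12.5) | .02 | 1.23 | 81 | 7.4% | 86% | 75% |
| 8 (12.5) | .05 | 1.58 | 63 | 11.4% | 76% | 64% |
| 8 (12.5) | .10 | 2.15 | 47 | 17.6% | 62% | 52% |

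Simulation with 20,000 trials per setting agrees. At ICC .02, .05 and .10, type I error is about 6%, 7% and 8–9% for 25 facilitators of 4 families; 7%, 10% and 15% for 10 of 10; and 7–8%, 11% and 17–18% for 8 of 12.

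**4. What part of the power loss is due to correlation?** At ICC 0, using (facilitators − 1) df alone lowers power from 92% to 90% (25 facilitators), 86% (10) or 83% (8). The last column of the table therefore mixes two costs: correlation, and few clusters.

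**5. Where 100 families stop giving 80% power.** The tolerable DEFF is 100/70 = 1.43, so the threshold ICC is .43/(m − 1). That is .14 for m = 4, .11 for m = 5, .048 for m = 10 and .037 for m = 12.5. With cluster-level df the thresholds are lower: about .02 for 10 facilitators and below .01 for 8.

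**6. Number of agencies.** At 20 retained per agency, 5 agencies give 100 families and 4 give 80. With 80 independent families power is 85%.

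**The case against.** The strongest reply is that everything depends on an ICC of change that the documents do not give. Pairing has already removed level differences, and the remaining correlation could be small. Caseload is also inferred: no section states families per facilitator or that every trained person delivers. The 8-facilitator case combines minimum staffing with the lower of two conflicting agency counts. All of this stands, and it makes the size of the problem conditional.

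A reader might infer that n = 100 is inadequate for d = .34. The documents do not support that. No target power is stated, unadjusted power is 92%, and with 25 facilitators power stays above 80% across the whole assumed range even with cluster-level df. Part of the loss with 8 or 10 facilitators comes from degrees of freedom rather than correlation.

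A reader might also infer that each family's own facilitator collects its outcome data, which would add correlated measurement. Outcomes {12}, Data collection methods {18a, 18b} and Data management {19} say that interventionists or agency providers film and administer the measures, but not that it is the family's own facilitator. Videos for the primary outcome are coded centrally at an outside university, which limits any facilitator effect through scoring. It does not remove variation in delivery.

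Finally, random-effect structure is often left to a statistical analysis plan. That would answer an omission, but this article names the tests, and a later plan could allow for clustering only by replacing or supplementing them.

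**Conclusion.** The point holds in conditional form. The named tests assume independent families, the stated staffing implies several families per facilitator, and nothing in the article allows for correlated change. If the ICC of change is positive, intervals will be too narrow and the type I error will exceed .05. At an assumed ICC of .02 to .10, it is about 6–9% with 25 facilitators and 7–18% with 8 to 10.

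The sufficiency statement lacks a power and any allowance for clustering. It may fail if few facilitators deliver and the ICC exceeds about .04 to .05 (lower with small-cluster df), but it is not shown to be wrong. The figures assume equal caseloads, delivery by all trained staff, and d on the SD of change. The change is worth making, but the point does not undermine the design.

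**What to change.** - **Data.** Record facilitator and agency ID for each family in REDCap, if this is not already done. Recruitment has begun, so this is best settled now.
- **Analysis {20a}.** For the primary outcome, replace the paired t-test and repeated-measures ANOVA with a linear mixed model: visit as a fixed effect, family as a random effect, and a facilitator random effect on change (facilitator-by-visit), with Kenward-Roger or Satterthwaite degrees of freedom. Cluster-robust errors with a small-sample correction are an alternative. If agency is included, use agency-by-visit, because an agency main effect alone does little for a pre/post contrast.
- **Sample size {14}.** Reconcile 4 versus 5 agencies. State the scale of d. Restate the detectable d with its power over ICC 0 to .10 and the planned number of facilitators, leaving n unchanged. By the design effect alone, the detectable d at 80% power is .28 at ICC 0; at ICC .10 it is .32 with 25 facilitators, .39 with 10 and .42 with 8.

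**Cost.** Some analysis wording, one or two ID fields, a somewhat wider interval and a less favourable detectable d. With only 8 to 10 facilitators the variance component will be imprecise. Agency-by-visit terms would use further degrees of freedom, leaving roughly 8 − 4 = 4 or 10 − 5 = 5 at minimum staffing, so the choice should be made in advance.

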### Objectives {7}

Building on input from community health and social service agency administrators and health and social service providers, our completed pilot work, and the urgent need for RF interventions to address impacts of toxic stress on vulnerable children in the community, this team aims to address two co-primary objectives, Thus, our EIH design (Type II) [29] addresses co-primary objectives in Effectiveness of Clinical Intervention (Objective 1) and Feasibility of Implementation Strategy (Objective 2). We will complete this work with the assistance of our Community Engagement Committee (CEC), Patient Engagement Committee (PEC) and Support for Patient Oriented Research (SPOR) Committee.

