#### Objective 1 (quantitative arm)

With quasi-experimental methods we will (1a) Evaluate ATTACH^TM^ impacts on parent-child relationship quality (primary outcome), parental reflective function, and child development; (1b) determine whether ATTACH^TM^ is equally effective across patient populations (and for whom it works best/worst); (1c) evaluate whether ATTACH^TM^ impacts immune biomarkers indicative of inflammatory disease risk, i.e. gene expression and DNA methylation; and (1d) evaluate the long-term impact of ATTACH^TM^ (3 months post-intervention).

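### Objective 1b sets out to determine for whom ATTACH works best or worst from an open list of subgroup tests, each at .05; it should be labelled exploratory and reported as interaction estimates

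*Protocol article*

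**What the plan says.** Objectives {7}, Objective 1 (quantitative arm), states the aim: "1b) determine whether ATTACH^TM^ is equally effective across patient populations (and for whom it works best/worst".

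Statistical methods {20a, 20b and 20c} repeats the aim and gives the method: "and for whom it works best/worst), we will examine differences among sub-groups derived from known covariates through use of independent samples *t*-tests", followed by ANOVA for factors with more than two groups, repeated-measures ANCOVA, and linear regression for continuous covariates. Its examples are child sex, race/ethnicity, age and years of education. The error rate is set at the head of that section: "For all analyses, alpha will be set a priori at .05 (two-tailed".

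The list of known covariates is not given. Data collection methods {18a, 18b} says that covariates will mainly be the toxic-stress measures (EDS, CTS2-SF, ASSIST, ACE), adds the BRS for resilience, and lists the demographic items: "ethnicity, sex, and gender, first language, marital status, education, employment, number of children, and age of patients and children".

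Sample size {14} plans for families who have "completed all study components with 100 new families" and justifies that number only for the whole-group change: "a sufficient *n* to detect minimum *d* = .34 for pre- /post- assessment differences in parent-child relationship quality". No power is stated, and no subgroup comparison is sized.

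**The concern.** Two stated choices do not fit together. The aim is worded as a determination, down to who benefits most and least. The method is a set of separate tests of open length, each judged at .05. The article neither calls 1b exploratory nor limits or orders the covariates.

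Followed as written, the plan gives a substantial chance of reporting that ATTACH works differently in some population when it does not. Picking out the best and worst groups adds a second problem, because it selects the extremes of noisy estimates. The programme is meant for integration into routine care at community agencies, so a spurious statement about who benefits least would be an unhelpful product of the trial.

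**Working it through.** **Inputs from the article.** Alpha .05 two-tailed for all analyses; 100 families, one group, pre/post; planned d = .34.

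**Assumptions, not in the article.** One outcome, the same true effect in everyone, subgroup tests made on the pre/post change, half/half splits, and d expressed on the SD of change. The number of tests k is shown for three readings:
- k = 5: the four toxic-stress measures plus the BRS.
- k = 9: those five plus the four examples in the analysis section.
- k = 14: those five plus about nine demographic items (sex and gender counted once; 13 to 15 is the plausible range).

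**The plan's own figure.** A paired t-test with n = 100, d = .34 and two-sided .05 has 92% power. It needs 70 families for 80% power and 93 for 90%. So 100 is enough for the whole-group comparison, although the figure cannot be derived exactly because no power is stated.

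**Step 1: false significance.** For independent tests, P(at least one) = 1 − 0.95^k.
- k = 5: 1 − 0.774 = 22.6%
- k = 9: 1 − 0.630 = 37.0%
- k = 14: 1 − 0.488 = 51.2%

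With equicorrelated test statistics (simulation, 200,000 draws), k = 5 gives 21.9% at correlation 0.2 and 18.2% at 0.5; k = 14 gives 47.4% and 35.0%. When the correlation is placed on the underlying covariates, a separate simulation of 14 half/half splits gives 42% at 0.5.

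**Step 2: chance spread between subgroups.** This does not depend on alpha. In SD-of-change units the standard error of a half/half contrast is √(1/50 + 1/50) = 0.20. Then P(|difference| ≥ .34) = 2[1 − Φ(.34/.20)] = 2[1 − Φ(1.70)] = 0.0891. Over k contrasts the chance is 1 − (1 − 0.0891)^k.

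| k | at least one false significance | at least one gap ≥ .34 |
|---|---|---|
| 5 | 23% | 37% |
| 9 | 37% | 57% |
| 14 | 51% | 73% |

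The last column passes 50% only from k = 8 (48% at 7, 53% at 8). For k = 14 it is 62% at covariate correlation 0.5, and 83% or 93% with 30/70 or 20/80 splits.

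**Step 3: dependence on the scale of d.** If d is on the raw-score SD and the pre/post correlation is 0.7, the SD of change is √(2 × 0.3) = 0.775, the standard error is 0.155 and the single-contrast probability is 0.028. The last column becomes 13%, 23% and 33%. At correlation 0.5 the SD of change equals the raw SD and nothing alters. Step 1 is unaffected.

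**Step 4: what a subgroup test can show.** A half/half contrast must reach 1.96 × 0.20 = 0.39 to be significant at .05, so any such finding is larger than the .34 for which the whole trial is sized. Power for a true subgroup difference of .34 is Φ(1.70 − 1.96) = 40%. With Bonferroni over 14 tests it is 11%. Multiplicity adjustment over a long list therefore does not make 1b able to determine anything.

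**The case against.** **The number of tests is not fixed.** This stands in part. Fourteen is an upper-end count. The article says covariates will mainly be the toxic-stress measures, names four examples, and says under Confidentiality {27} that demographic data serve to describe the sample. Five or nine is as defensible, which is why the range is shown. Even at five the error is 18% to 23%.

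**Chance will not usually yield a best and a worst group .34 apart because each test is at .05.** A reader might infer that it will. The article does not support this: the size of an observed gap does not follow from the alpha level, the chance exceeds one half only from about eight half/half contrasts, and it depends on the scale of d. Continuous covariates analysed by regression form no groups at all, and a factor with several levels tested by ANOVA is falsely significant in only 5% of trials, however wide its gap.

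**1b is not a co-primary hypothesis.** A reader might infer that it is from "addresses co-primary objectives in Effectiveness of Clinical Intervention (Objective 1) and Feasibility of Implementation Strategy (Objective 2". That phrase describes the effectiveness and implementation domains of a Type II hybrid design. The article names one primary outcome, under 1a, and sizes the trial on it alone.

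**The analysis plan may settle this.** Subgroup lists and multiplicity handling are often left to it, and none is shown. The objection does not dispose of the point, because the article itself fixes both the alpha for all analyses and the determinative aim. A later exploratory label would have to change that text.

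**No ranking procedure is described.** True: best/worst appears in the aim, while the method only examines differences. Nor does the article say that agencies would ration the programme on the result. The concern is with what the aim invites.

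**Conclusion.** The point holds in a limited form. Followed as written, 1b carries a chance of at least one false subgroup finding of about 23%, 37% or 51% for 5, 9 or 14 independent tests on one outcome, lower with correlated tests (18% and 35% for 5 and 14 at correlation 0.5). Independently of that, the order of subgroup means from 100 families is a poor guide to who benefits: a gap of .34 arises by chance in about 37%, 57% or 73% of trials on the SD-of-change scale, and less often on the raw-score scale with a high pre/post correlation. The figures rest on no true heterogeneity, half/half splits and a covariate count that the article leaves open. Testing the reflective-function and ASQ-3 outcomes as well would raise the first set. The whole-group pre/post comparison is not affected.

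**What to change.** - In Objectives {7} and in the analysis of 1b, state that 1b is exploratory and hypothesis-generating.
- Replace the aim of determining who benefits most and least by estimating covariate-by-visit interactions on the primary outcome. Report them with confidence intervals for all covariates examined, and make no claim from ranking subgroups.
- In the opening of Statistical methods, exempt 1b from the unadjusted .05 decision rule.
- If a confirmatory subgroup claim is wanted, limit it to a short list fixed in advance, for example the four toxic-stress measures already named as the main covariates, with Holm adjustment (the smallest p-value is then judged at .05/4 = .0125).

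The change is to wording and uses data already planned. Its price is weaker subgroup statements, which is what 100 families can support.

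### Objective 1b asks whether ATTACH works equally well across patient populations, but the tests named for it can only show that effects differ

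*Protocol article*

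**What the plan says.** Under Objectives {7}, part (1b) is to "determine whether ATTACH^TM^ is equally effective across patient populations (and for whom it works best/worst"). The objective has two halves: whether effects are equal, and where they are largest and smallest. Statistical methods {20a, 20b and 20c} repeats it and names the method: "we will examine differences among sub-groups derived from known covariates through use of independent samples *t*-tests" for two groups such as child sex, ANOVAs for more than two groups such as race/ethnicity, repeated measures ANCOVA with an identified covariate, and linear regression for continuous covariates such as age or years of education. One error rate covers everything: "For all analyses, alpha will be set a priori at .05 (two-tailed").

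Sample size {14} justifies 100 families as "a sufficient *n* to detect minimum *d* = .34 for pre- /post- assessment differences in parent-child relationship quality". That is the overall comparison. No power is claimed for subgroups, and no subgroup sizes are given.

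**The concern.** The first half of 1b is a question about equality, and every method listed for it looks for a difference. A significant result would answer it in the negative. A non-significant result would leave it open, because it is compatible both with equal effects and with a gap that 100 families cannot resolve. With no margin and no interval criterion, the plan gives no valid route to a positive answer.

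A second problem is what the tests act on. The text speaks of differences among subgroups without saying in what. An independent-samples t-test or ANOVA on scores compares levels between groups. Groups can differ in level and gain the same amount, or share a level and gain different amounts. Only a comparison of change, or a covariate-by-visit interaction, addresses whether the effect differs.

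At stake is what the trial may conclude about who benefits.

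**Working it through.** **Inputs.** From the protocol: 100 families completing all components, d = .34 for the pre/post difference (Sample size {14}), and alpha .05 two-sided (Statistical methods). Assumed, because the protocol does not say: d is in SD of change, the SD of change is 1 in each subgroup, and two subgroups split 50/50, 30/70 or 20/80.

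**The plan's own figure first.** Paired t-test, n = 100, d = .34: noncentrality = .34 × √100 = 3.4 on 99 df, power 92%. The overall claim of sufficiency is sound. An exact match cannot be tested because the protocol states no power.

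**Precision of a subgroup difference in change.** Standard error = √(1/n1 + 1/n2). 95% CI half-width = t(.975, 98) × SE, with t = 1.984. Power for a gap of .34 comes from the noncentral t with noncentrality .34/SE on 98 df.

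| Split | SE | 95% CI half-width | Power for a gap of .34 | Gap detectable with 80% power |
|---|---|---|---|---|
| 50/50 | .200 | .40 | 39% | .57 |
| 30/70 | .218 | .43 | 34% | .62 |
| 20/80 | .250 | .50 | 27% | .71 |

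In every row the half-width exceeds .34. At 50/50 an observed difference of exactly zero has a 95% CI of about −.40 to +.40, which includes a gap of .34 in either direction.

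**More than two groups.** With 100 families in equal groups, two extreme groups .34 apart and the rest midway, one-way ANOVA on change has power 21% (3 groups), 14% (4) and 11% (5).

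**Could equality be tested instead?** Two one-sided tests at 5% each, with an illustrative margin of .34 and a true gap of zero: power at 50/50 ≈ 2Φ(.34/.20 − 1.645) − 1 = 2Φ(.055) − 1 ≈ 4%. For 80% power, n per group = 2 × ((1.645 + 1.282)/.34)² ≈ 148.2, so 149 per group or 298 families.

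**Sensitivity to the scale of d.** If .34 is in raw-score SD units with pre/post correlation r, the gap in SD of change is .34/√(2(1 − r)), and the 50/50 CI half-width in raw SD is .397 × √(2(1 − r)).

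| r | Gap in SD of change | Power, 50/50 | CI half-width, raw SD |
|---|---|---|---|
| 0 | .24 | 22% | .56 |
| .3 | .29 | 30% | .47 |
| .5 | .34 | 39% | .40 |
| .7 | .44 | 58% | .31 |
| .8 | .54 | 76% | .25 |

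On that reading, with r of about .7 or more, an observed zero at 50/50 would exclude a gap of .34. The numerical part therefore depends on the scale. The mismatch between question and test does not.

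**The case against.** Four points on the other side carry weight.

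- **Half of 1b is about differences.** Tests of difference suit the question of where the programme works best or worst. This stands; the mismatch concerns the other half.
- **The method list is fuller than t-tests.** Repeated measures ANCOVA can address change, and regression already keeps continuous covariates continuous. Coding of interaction terms is normally left to an analysis plan. This stands in part: the t-tests and ANOVAs remain untied to change. The objective and the tests are both fixed in this article, so a later plan that kept both would keep the mismatch.
- **No subgroup power is promised.** The sample size is justified only for the overall pre/post difference, so low subgroup power breaks no stated claim. This stands, and the figures above serve only to show what 1b can support.
- **The .34-versus-zero gap is only one scenario.** At 50/50 it averages .17 overall, not .34. If the overall effect is .34 and half the families gain nothing, the other half gains .34/.5 = .68, and power for that gap is 92%. If 30% gain nothing, the gap is .34/.7 = .49 and power is 60%. If 20% gain nothing, it is .34/.8 = .43 and power is 39%.

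For this last reason a reader should not take 1 − .39 = .61 as a general rate at which 1b would miss a group that does not benefit. It holds for one gap, one split and one reading of d. A reader might also infer that the investigators will report a null result as equal effectiveness and that agencies will act on it. The protocol contains no such decision rule and says nothing about agencies using subgroup results.

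**Conclusion.** The point holds as a mismatch between the stated question and the stated method: tests of difference at .05, without a margin or interval criterion, cannot establish that ATTACH is equally effective across populations. This part needs no assumption.

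Its size rests on reading d = .34 in SD of change, which is natural for a paired comparison but not stated, and on assumed splits of the 100 families. On that basis a subgroup difference in change is known only to within about ±.40 to ±.50 SD, so a gap of .34 could not be excluded even if none were observed. Large gaps, about .57 or more at an even split, would be found with at least 80% power. The overall pre/post comparison is unaffected. This should be changed, since it alters what the trial may conclude and costs little.

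**What to change.** - **Objectives {7}, (1b).** Reword as exploring whether change differs by subgroup, and in which groups change is largest or smallest.
- **Statistical methods, (1b).** Estimate each moderator as a covariate-by-visit interaction, or by comparing change scores, rather than by comparing score levels. Keep the regression approach already planned for continuous covariates.
- **Reporting.** Give each difference in change with its 95% CI and label the analysis exploratory. State that a non-significant difference will not be reported as equal effectiveness.

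The cost is the wording of one objective and a few lines of analysis text, with no extra families, visits or measures. The downside is giving up an equality claim that the data could not support. Keeping the claim would need a margin fixed in advance, and at the illustrative margin of .34 SD of change 100 families would almost never meet it.
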